##### Self-reported health and psychosocial measures

Participants will be asked to complete measures of their self-reported health and psychosocial measures, using existing and validated measures were available. Wellbeing will be measured using the Cantril ladder [38]. Self-esteem will be assessed by the 10 item version of the Rosenberg self-esteem questionnaire [39], in which participants rate each statement on a 4-point Likert scale (ranging from ‘strongly agree’ to ‘strongly disagree’). Vitality [40] will be measured using four statements (i.e. ‘I felt alive and vital’; ‘I had energy and spirit’; ‘I nearly always felt alert and awake’; and ‘I felt energised’) on a 7-point scale (ranging from ‘not at all true for me’ to ‘very true for me’). Health-related quality of life will be measured using the EQ-5D-5 L [41]. This is a standardised instrument for use as a measure of health outcomes. Participants rate their mobility, self-care, usual activities, pain/discomfort and anxiety/depression on a 5-point scale. They also rate their health today on a scale from 0 to 100.

In a face-to-face structured interview with a member of the fieldwork staff, participants will be asked to report joint pain, and any long standing illnesses, disabilities or infirmities. Injuries that occurred before and during the EuroFIT trial will also be recorded during this interview.

##### Self-reported socio demographic measures

The self-reported questionnaire will assess demographic characteristics (age, ethnicity, education, marital status, current employment status, income) at baseline. These characteristics will be used as potential moderators of any intervention effects on behavioural and other outcomes, to identify whether the program is more or less beneficial for pre-specified subgroups of men.

##### Self-reported mediators

Motivation for physical activity will be assessed using the adapted Behavioural Regulation In Exercise Questionnaire (BREQ-2) [42]. This questionnaire consists of 15 statements which require a response on a 5-point scale (range ‘not true for me’ to ‘very true for me’); these assess participants’ intrinsic motivation, identified regulation, introjected regulation, external regulation and amotivation in relation to exercise. Participants will also complete six items related to ego/task involvement [43–45], allowing us to explore participants’ motivational criteria for what it takes to succeed according to their own goals. These will be used in part to compare the variance between those that engage with the program to those who do not. The self-reported questionnaire also includes the Sport Spectator Identification Scale which contains seven Likert-scale items assessing identification with a sports team (response options range from 1 (low identification) to 8 (high identification)) to measure men’s degree of identification with their football club [46].

To assess the potential contribution of other weight loss activities, we will ask participants to report if they did anything else to lose weight (such as attending exercise workouts, attending a commercial weight loss program, having weight reduction surgery). Participants will also be asked to report what sort of strategies (i.e. eating breakfast on a daily basis, limiting quantity, restricting intake of certain foods, drinking fewer sugary drinks or less alcohol and consciously eating more slowly) they use to manage their weight on a 5-point scale ranging from ‘never’ to ‘always’.

We will also assess the extent to which EuroFIT participants report that coaches and other group members were able to create a needs-supportive motivational climate. Specifically, we will measure the extent to which participants report that coaches were able to support their autonomy, competence to make changes, and feelings of relatedness, using a 5-point scale ranging from ‘not true for me’ to ‘very true for me’ [47]. We will also measure ‘thwarting’ of autonomy, competence, and relatedness needs by the coach using a 9-item measure adapted from Bartholomew et al. (2011) which are rated on a 7-point scale ranging from ‘strongly disagree’to ‘strongly agree’ [48]. In addition, six items will assess the extent to which men feel the group climate supported mastery and performance rated on a 7-point scale ranging from ‘not at all true’ to ‘very true’ [49]. Relatedness need satisfaction *from the group* will be measured by 6-items adapted from Van den Broeck et. al. (2010), and rated on a 7-point scale ranging from ‘not at all true’ to ‘very true’ [50]. Finally, at 12 months only, we will ask participants to rate the satisfaction they experienced from engaging in physical activity on a 6-point scale (range ‘false’ to ‘true’) drawn from the adapted psychological needs satisfaction in exercise scale [51].

### Economic evaluation

This study will include an evaluation of the cost-effectiveness of EuroFIT in comparison to receipt of a healthy lifestyle leaflet only at 12 months (short-term within trial) and a projected 5 years (long-term modelling) with regard to the primary outcomes of the trial and quality of life.

A Health and Personal Social Service perspective, as well as a societal perspective, will be employed. Data on resource utilisation will be collected using self-report questionnaires based on the iMTA Productivity Cost and Medical Consumption questionnaires (iPCQ and iMCQ) [41] and will include utilisation of healthcare services, medication use and absenteeism from paid work. Medication use will be measured at baseline and after 12 months. Utilisation of healthcare services and absenteeism from paid work costs will be measured post-program, at 6 months and at the 12-month follow-up. Researchers will send participants an email to ask them to complete the 6-month questionnaire online. Men who do not have an email address will be sent a paper version of the questionnaire by post and a reply-paid envelope.

### Process evaluation

A process evaluation will be embedded in the RCT to provide insight into whether the EuroFIT program is delivered as intended, why it did or did not produce the intended outcomes, and how such a program can be delivered within the specific context of a professional football club in future. We will investigate the processes that are necessary for implementation of the EuroFIT program, the way in which the program operates on outcomes and on any unintended outcomes, and participants’ and coaches’ experiences of the program. At both post-program and 12 month follow-up measurements, the intervention group will be asked to complete self-report questions focusing on: experiences with the program; SitFIT and MatchFIT usage; which elements of EuroFIT they found most useful; the extent to which they are still interacting with their EuroFIT peers after the program has ended; and the perceived impact of the EuroFIT program on their lives. The design of the process evaluation is described in a separate study protocol.

### Database

The Robertson Centre for Biostatistics (RCB), University of Glasgow, within the Glasgow Clinical Trials Unit, will oversee RCT data management.

All trial subject data will be entered locally in each country via the study web portal, which features an online data entry system with data validation checks built in. Data will be entered either via a web-portal or a tablet app. All data will be stored securely on the local servers of the RCB. All personal data will be anonymised and encrypted; it will only be possible to link back to an individual via a separately-stored encrypted coding system. Paper data and identifiers will be held in secure locked locations on local University premises. At the end of the trial, final data validation checks will be carried out prior to database locking and unblinding of random group assignment.

### Data analyses

The RCB will provide statistical services in support of delivering the RCT. A detailed Statistical Analysis Plan will be developed, and finalised prior to database lock and unblinding. RCB statisticians will develop analysis programs during the trial, whilst blind to randomised allocations, and communicate any data anomalies to RCB data managers and to the project team at each site for checking.

#### Sample size calculations

The study is powered to detect small, but clinically relevant, changes in the primary outcomes: objectively measured (using the activPAL device) total physical activity (e.g. daily step count) and total sedentary time at 12 months.

Both primary outcomes are powered (separately, not as a composite primary outcome) at 90 % to detect an effect size of 0.25 standard deviation (SD) units at a 2.5 % significance level. In relation to physical activity, which has a standard deviation of approximately 4000 steps per day, the trial will be powered to detect an average increase of at least 1000 steps per day (roughly equivalent to 10 min of moderate intensity physical activity on average per day). In relation to sedentary time, which has a SD of almost 100 min/day [52], the trial is powered to detect an average decrease of at least 25 min per day spent sitting. A sample size of 400 per group will allow us to detect these changes. To achieve this sample size at 12 months we estimate that we will need to include a total of 1000 eligible participants in the RCT.

In relation to blood-based biomarkers, we estimate that >70 % of participants will opt-in to blood sampling (>245 in each arm), which will provide 90 % power, at 5 % significance, to detect an effect size of 0.29 SD units for a normally-distributed outcome measure. Fasting insulin is the biomarker of principal interest; its SD in non-diabetic adults is ~6 mU/l (87), thus the study will be powered to detect a change in fasting insulin with the EuroFIT intervention of at least ~1.7 mU/l.

#### Effectiveness analysis

In accordance with the study aims, statistical analyses will be conducted to determine whether the intervention group differs from the comparison group in changes over time in primary and secondary outcomes. The key analysis will be undertaken on an intention-to-treat basis, regardless of individual engagement with the EuroFIT program. However, further sensitivity analyses will determine the association between attendance at intervention sessions and effectiveness. Analysis of outcomes at each time point will use linear mixed effects regression methods (normal, logistic or other generalised linear models, as required), including random effects for country and football club, and fixed effects for study group and baseline measurement of the outcome. Regression models will be extended to assess moderators and mediators of intervention effects. The patterns and extent of missing data will be examined and, if necessary, methods such as multiple imputation will be implemented to provide robust results for primary and main secondary outcomes, assuming data are missing at random.

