Self-monitoring of physical activity with a pedometer is an effective strategy to improve physical activity behaviour [24, 25], and proved to be very popular amongst men as one element of the FFIT program [23]. In light of this, EuroFIT has developed the SitFIT, a pocket-worn activity and sedentary/non-sedentary behaviour monitor. The SitFIT provides real time feedback on both step counts *and* upright (non-sedentary) time and so allows participants to actively self-monitor their daily physical activity (steps), sitting time and upright time (time spent standing and walking). Participants use their SitFIT to track their progress against an individualised, incremental program to increase both their daily step count and time spent upright. The SitFIT can also display steps and upright time data over the past seven days, and each participant can obtain a more detailed historical record of his SitFIT data via computer upload (PC and MAC) to the MatchFIT app. MatchFIT has been developed as part of the EuroFIT study to enable between-session social support via a chat function, and provides a competitive element where each club-based EuroFIT group can compete collectively in a step challenge against a computer-generated football team, using an algorithm which takes account of the group’s previous week’s step performance. It should be noted that the competitive element is not a person-to-person competition. Rather, the competition is group-based to enhance the social support aspect of the program.

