### Randomisation

We will be using an individually randomised design, as was used in the FFIT RCT, which confirmed that the higher sample size and costs associated with a cluster randomised design were unwarranted as minimal contamination was observed between intervention and comparison group participants (the mean difference in weight loss between groups adjusted for baseline weight and club was 4.9 kg [95 % CI 4.0,5.9]; a sensitivity analyses adding club as a random effect adjusted for baseline weight to account for possible clustering gave 4.9 kg [95 % CI 3.8,6.0]) [14, 29].

Participants will be randomly allocated to the EuroFIT intervention group or the waiting list comparison group in a 1:1 ratio, stratified by football club. The method of randomised permuted blocks will be used, with random block lengths (4 or 6). The randomisation schedule for each club will be generated by a computer program and stored within the Clinical Trials Unit, with access restricted to those responsible for maintenance of the randomisation system. Research staff in each country will not have access to randomisation codes during baseline data collection; when baseline data have been collected, local research staff will access the random allocation for each individual via a study web portal. Data management and statistical staff within the Clinical Trials Unit will not have access to randomisation codes prior to database lock, with the exception of statistical staff providing reports to the Independent Data Monitoring Committee; these staff members will not be involved in the development and implementation of the final statistical analyses.

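### The stated effectiveness model has no term for correlation among intervention men treated together in groups, and the sample size makes no allowance for it

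*Protocol article*

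**What the plan says.** Under Effectiveness analysis, outcomes at each time point are analysed by mixed effects regression, "including random effects for country and football club, and fixed effects for study group and baseline measurement of the outcome". No delivery-group, coach or club-by-arm term is named.

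Under Randomisation, allocation is individual, 1:1 and stratified by club. The section on the EuroFIT program describes twelve weekly coach-led group sessions for the intervention arm, built on peer interaction and mutual support. Through the app, "each club-based EuroFIT group can compete collectively in a step challenge", and steps are one of the two primary outcomes. The comparison arm receives a leaflet and a place on a waiting list.

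Under Sample size calculations, each primary outcome is powered "at 90 % to detect an effect size of 0.25 standard deviation (SD) units at a 2.5 % significance level", and "A sample size of 400 per group will allow us to detect these changes". No ICC, group size or design effect is given.

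The Randomisation section supports individual randomisation by the low contamination seen in the earlier FFIT trial. It adds that "a sensitivity analyses adding club as a random effect adjusted for baseline weight to account for possible clustering gave 4.9 kg", with a 95 % interval of 3.8 to 6.0, against 4.0 to 5.9 from the analysis adjusted for baseline weight and club.

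**The concern.** This is a partially nested design: individual randomisation, with grouping created by treatment in one arm only. Men who share a coach, a group and a collective step target may end up more alike at 12 months than men on a waiting list. The article presents such interaction as a way the programme works.

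A random intercept for club describes what all men of a club share, whichever arm they are in. That part drops out when treated and comparison men are compared within the same club. What remains, and what the stated model sets to zero, is variation in the treated men's average from group to group. Counting that variation as independent individual noise understates the standard error of the treatment effect. At stake are the 2.5 % error level set for each primary outcome, the coverage of the intervals, and the meaning of the 90 % power statement.

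**Working it through.** **Inputs from the article.** Effect 0.25 SD; significance level 2.5 %, taken as two-sided because that reproduces the sample size; 90 % power; 400 analysed per group; 1000 randomised; 15 clubs; 1:1 allocation within club.

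**Inputs assumed, because the article does not give them.** Treated-arm ICC of 0.01, 0.02 or 0.05; one or two delivery groups per club; where used, a baseline-to-outcome correlation r of 0.5.

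**Step 1: reproduce the stated figure.** n per group = 2 × ((2.2414 + 1.2816) / 0.25)² = 397.2. Power at 400 = Φ(0.25 × √(400/2) − 2.2414) = Φ(1.294) = 90.2 %. The total follows as 800 / 0.80 = 1000. So 400 is the independent two-sample number, and the step to 1000 covers a 20 % loss and nothing else.

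**Step 2: variance with treated-arm clustering.** Analysed men per delivery group: m = 400/15 = 26.7 (one group per club) or 13.3 (two). Only the intervention arm carries the design effect 1 + (m − 1) × ICC. The variance ratio for the contrast is therefore V = [1 + (m − 1) × ICC + 1] / 2. Example, one group and ICC 0.05: V = (2.283 + 1) / 2 = 1.642.

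**Step 3: type I error of the stated model.** In a balanced layout a shared club intercept leaves the model's standard error close to its independent value, so the actual error is about 2 × (1 − Φ(2.2414 / √V)). Simulation of 15 clubs with 27 analysed men per arm per club gives slightly higher values, because the model's residual variance is itself a little too small. Repeat runs agree to within about 0.2 percentage points. At ICC 0 the simulation returns about 2.5 %.

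**Step 4: power when the variance is correct.** Power = Φ(0.25 / √((1 − r²) × 2V / 400) − 2.2414), with r = 0 or 0.5.

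| Groups per club | ICC | V | Type I error, formula | Type I error, simulation | Power, r = 0 | Power, r = 0.5 |
|---|---|---|---|---|---|---|
| 1 | 0.01 | 1.128 | 3.5 % | 3.6 % | 86 % | 95 % |
| 1 | 0.02 | 1.257 | 4.6 % | 4.9 % | 82 % | 92 % |
| 1 | 0.05 | 1.642 | 8.0 % | 8.3 % | 70 % | 83 % |
| 2 | 0.01 | 1.062 | 3.0 % | 3.0 % | 88 % | 96 % |
| 2 | 0.02 | 1.123 | 3.4 % | 3.6 % | 86 % | 95 % |
| 2 | 0.05 | 1.308 | 5.0 % | 5.1 % | 80 % | 91 % |

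The r = 0.5 column applies the same reduction to the between-group and within-group variance.

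**Step 5: coverage.** In simulation, nominal 97.5 % intervals from the stated model covered the true effect in about 96.5 / 95.2 / 91.9 % of trials with one group per club, and 97.1 / 96.5 / 94.8 % with two, at ICCs of 0.01 / 0.02 / 0.05.

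**The case against.** The strongest reply is that the size of the problem is assumed. Neither the ICC nor the number of groups is in the article. The primary endpoint is at 12 months, long after the weekly sessions end, so correlation may have faded. If the programme changed no man's behaviour, delivery would induce no correlation and the test would keep its level. All of this stands as a limit: inflation is conditional, and the figures are a range. It does not rescue the model. Groups can differ in benefit around any average effect, and interval coverage then falls short whether or not that average is zero.

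A second reply is that the article says random effects, not intercepts only, and defers detail to an analysis plan that is not shown. That plan may add an arm-specific term. But the article does state a model, and in it study group appears as a fixed effect only.

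A third reply is that the sample size takes no credit for baseline adjustment, which the model includes. This also stands: with r = 0.5, power is 83 to 96 % across the cases above. Adjustment does not, however, correct the standard error or the error rate.

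Two stronger readings are tempting. A reader might take the FFIT intervals, 1.9 and 2.2 kg wide, as a variance ratio of (2.2/1.9)² = 1.34 and infer power of about 79 % here. The article does not support that. The outcome was weight, the sensitivity model is not described beyond a club random effect, and rounding alone allows 1.10 to 1.63. If a club random effect cancels, as argued here, that widening cannot be read as a measure of treated-arm clustering. A reader might also infer that the Randomisation section calls clustering negligible. It does not. It argues that contamination was minimal and reports the wider interval openly. One may note only that the quoted intervals bear on clustering, not on contamination.

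**Conclusion.** The point holds as a conditional one. The stated model, read plainly, has no place for correlation confined to the intervention arm, and its standard error is too small whenever that correlation is above zero. With assumed ICCs of 0.01 to 0.05, the error rate for each primary outcome lies roughly between 3.0 and 8.3 % against 2.5 % nominal, depending also on whether a club runs one or two groups. It cannot be said that the error rate certainly exceeds 2.5 %.

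It is certain that the 400 per group contains no allowance for clustering. Whether true power falls below 90 % is open, because it depends on the ICC, the group size and the baseline correlation. The error rate and the coverage are therefore the firmer part of the point. Individual randomisation itself is not in question.

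**What to change.** In the primary and secondary models, add a random effect for delivery group, or for club-by-arm, that acts in the intervention arm. Use Kenward-Roger or Satterthwaite degrees of freedom, since there are only 15 clubs. Restate the power with an assumed treated-arm ICC, the expected group size and an assumed baseline correlation, showing a range.

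No additional men need be enrolled and trial conduct does not change. The work is model wording and a recalculated power statement. Delivery group must be available in the analysis data. The article says the analysis plan is finalised before database lock and unblinding, so the term can be pre-specified there. The cost is somewhat wider intervals.

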### Cost-effectiveness analyses

Cost-effectiveness of the EuroFIT program in comparison with the comparison group will be evaluated at 12 months follow-up. Further, using data from the randomised controlled trial and epidemiological data, the long-term cost-effectiveness of the EuroFIT program in comparison with the comparison group will be modelled over a period of 5 years.

#### 12-month cost-effectiveness

Incremental Cost-Effectiveness Ratios (ICERs) will be calculated by dividing differences in costs between the groups by the differences in primary outcomes and Quality-Adjusted Life-Years (QALYs). Differences in costs and effects will be analysed using linear multilevel regression analyses. Clustering at the level of the football club will be included in these multilevel models. To estimate statistical uncertainty, 95 % confidence intervals will be estimated around cost and effect differences using bias-corrected bootstrapping with 5000 replications [53]. To account for the clustering of data, bootstrap replications will be stratified by football club [54].

To graphically illustrate the uncertainty around the ICERs, bootstrapped incremental cost-effect pairs will be plotted on cost-effectiveness planes [55]. A summary measure of the joint uncertainty of costs and effects will be presented using cost-effectiveness acceptability curves (CEACs). CEACs show the probability that the intervention is cost-effective in comparison with the comparison group at different ceiling ratios (i.e. the maximum amount of money decision-makers are willing to pay per unit of effect) [56].

